### Statistical analysis

A formal statistical analysis plan will be prepared by both an independent statistician and the principle investigator ahead of the final data collection (both blinded to treatment allocation and the study results). The final study findings will be released by the study statistician. Data analysis will be performed in patients who will receive RLN LND according to the procedure assigned at randomization and who will have complete follow-up data on nerve palsy recovery status at the 6-month assessment (for confirmation of permanent nerve palsy). A small percentage of patients (estimated 5% maximum) are expected not to undergo the procedure assigned at randomization either because of self-withdraw from the study or because of occurrence of unexpected intraoperative findings (as described in the “Surgical approach” section). Another 5% of patients may potentially be lost to follow-up, resulting in a maximum expected total dropout rate of 10%. We will perform both an in-depth analysis of the reasons for dropout and a comparison of dropouts and completers. The primary outcome will be analyzed using a two-sample proportion test (single-sided). Categorical secondary outcomes will be expressed as frequencies and compared with the Fisher’s exact test. Continuous secondary outcomes will be given as means ± standard deviations (for normally distributed variables) or medians and interquartile ranges (for skewed parameters). Comparisons will be performed using Student’s *t* test and the nonparametric Mann–Whitney *U* test, respectively. The Cochran–Mantel–Haenszel test will be used to examine the differences in categorical outcomes between the two treatment groups after adjusting for study center and use of nCRT. All calculations will be conducted with SAS (version 9.3; SAS Institute Inc., Cary, NC, USA) and SPSS (version 20.0; SPSS Inc., Chicago, IL, USA) statistical packages. *P* < 0.05 will be considered statistically significant.

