### Randomization

A computerized randomization tool will be used to randomly allocate patients to either RE or VATE (1:1 ratio). In order to minimize the potential confounding effect of local treatment variables (e.g., postoperative care), patients will be stratified in a 1:1 fashion according to the enrolling hospital. A permuted-block randomization with varying block size will be implemented. Allocation and block size will be concealed from all investigators. Blinding of surgeons is unfeasible because of the obvious technical differences between RE and VATE. However, the occurrence of the study endpoints will be determined from medical records by an independent assessor who will be blinded to the surgical technique used for each case. Patients will have the option to withdraw from the study at any time.

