### Surgical approach

Regardless of the treatment arm (i.e., RE versus VATE), all patients will undergo a total two-field lymphadenectomy according to the consensus proposed in 1994 by the International Society of Disease of Esophagus (ISDE) [22]. The operating surgeon will be exempted from performing RLN LND in the presence of at least one of the following conditions: low surgical curability as evidenced by tumor ingrowth into adjacent organs (i.e., T4b status) or unexpected detection of distant metastases (i.e., M1 status) during surgery; and/or occurrence of previously unforeseen perioperative adverse events and/or findings which will require discontinuation of surgery (all of these events will be detailed on an individual basis). Other surgical variables—including the use of laparotomy versus laparoscopy, the technique used for anastomosis, and the route of reconstruction—are not expected to influence the results of RLN LND and will be left to the surgeon’s discretion.

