### Follow-up schedule

Randomization will be considered the start of the study for each participant. All patients will be followed up according to the schedule shown in Fig. 2. The primary study endpoint will be assessed at 1 week (in the entire study cohort) and 6 months (in the subgroup of patients with confirmed postoperative left side RLN palsy at 1 postsurgical week). Data on postoperative complications, readmissions, and deaths occurring within 30 and 90 postoperative days will be collected. The study visits are planned at the following time points: 2 weeks before surgery; 4 weeks, 3 months, and 6 months after surgery; and every 6 months thereafter (until 5 postoperative years).

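### The only stated analysis population excludes patients after randomization on conditions that can depend on outcome, so the primary RE versus VATE comparison can be biased in either direction

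*Protocol article*

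**What the plan says.** The Statistical analysis section of the protocol article defines the population by two conditions. The first concerns treatment: "Data analysis will be performed in patients who will receive RLN LND according to the procedure assigned at randomization". The second concerns completeness of data and limits the set to those "who will have complete follow-up data on nerve palsy recovery status at the 6-month assessment". No analysis of all randomized patients is named, and the sentence is not limited to the primary outcome.

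The same section anticipates the losses. "A small percentage of patients (estimated 5% maximum) are expected not to undergo the procedure assigned at randomization", through withdrawal or through the intraoperative findings listed under Surgical approach. A further 5% may be lost to follow-up, for a maximum of 10%. The stated response is descriptive: "We will perform both an in-depth analysis of the reasons for dropout and a comparison of dropouts and completers".

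Three other sections matter:

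- Surgical approach releases the surgeon from the RLN dissection for T4b or M1 disease, or for "occurrence of previously unforeseen perioperative adverse events and/or findings which will require discontinuation of surgery".
- Randomization states that "Blinding of surgeons is unfeasible because of the obvious technical differences between RE and VATE".
- Follow-up schedule sets the primary endpoint assessment at 1 week for everyone and at "6 months (in the subgroup of patients with confirmed postoperative left side RLN palsy at 1 postsurgical week".

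Under Primary outcome measure, a patient is unsuccessful if pathology finds no left RLN nodes, or if left palsy persists at 6 months.

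**The concern.** In a superiority trial, randomization protects the comparison only while patients stay in the arm to which they were allocated. Both conditions here are settled after allocation, and each can be tied to the outcome.

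- **Receipt of the dissection.** If an adverse event leads the surgeon to omit it, no left RLN nodes are removed. That matches the node component of failure, yet the patient leaves the denominator. Such an event could be a consequence of the technique under test, and the surgeon knows the arm.
- **Complete 6-month palsy data.** Because the 6-month endpoint assessment is scheduled only after week-1 left palsy, missing data fall mainly on patients at risk of the palsy component. A patient who has already failed on the node component can also be dropped for want of palsy status, although the primary outcome is known.

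At stake is the primary result: unequal, outcome-related exclusions could produce an apparent advantage for RE or mask a real one.

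**Working it through.** **The plan's own figure.** Success of 70% versus 85%, one-sided alpha 0.05, power 80%, 1:1, pooled variance, no continuity correction:

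n = [1.645·√(2·0.775·0.225) + 0.842·√(0.70·0.30 + 0.85·0.15)]² / 0.15² = 94.8, so 95 per arm.

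95/0.9 = 105.6, so 106 per arm and 212 in total. Both stated figures reproduce. The 75% VATE rate named in the text, with 90% for RE, gives 79 by the same formula. That is a separate matter, but it is why both pairs of rates are used below. The null tested throughout is no difference, the one that reproduces 95.

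**Method.** Let F be the true failure rate among all randomized patients, e the share excluded and f the failure rate among the excluded. Then:

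- Failure rate among those analysed = (F − e·f)/(1 − e).
- Patients analysed per arm = 106·(1 − e).
- Probability of a significant result for RE = Φ[(gap − 1.645·SE0)/SE1], with SE0 the pooled and SE1 the unpooled standard error.

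The document gives the overall maxima (5% + 5% = 10%). The split between arms and f are assumptions.

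**Creating an effect.** True failure 25% in both arms:

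| Excluded RE / VATE | f in RE / VATE | Analysed failure RE / VATE | Gap (points) | False-positive rate |
|---|---|---|---|---|
| 5% / 5% | equal | equal | 0 | 0.05 |
| 8% / 2% | 0.5 / 0.5 | 22.8% / 24.5% | 1.7 | 0.09 |
| 6% / 4% | 1 / 1 | 20.2% / 21.9% | 1.7 | 0.09 |
| 5% / 5% | 1 / 0.25 | 21.1% / 25.0% | 3.9 | 0.16 |
| 8% / 2% | 1 / 1 | 18.5% / 23.5% | 5.0 | 0.22 |
| 10% / 10% | 1 / 0.25 | 16.7% / 25.0% | 8.3 | 0.41 |

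Fifth row in full: RE (0.25 − 0.08)/0.92 = 0.185; VATE (0.25 − 0.02)/0.98 = 0.235; gap 0.050; 97.5 and 103.9 patients; SE0 0.0575, SE1 0.0572; Φ[(0.0499 − 0.0946)/0.0572] = Φ(−0.78) = 0.22.

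**Hiding an effect.** True success 75% versus 90%, VATE exclusions all failures, RE exclusions average. At 5% per arm, VATE success among those analysed is 0.75/0.95 = 78.9%, the gap is 11.1 points and power is 0.70. At 10%, VATE is 0.75/0.90 = 83.3%, the gap is 6.7 points and power is 0.39. With uninformative exclusions of 10% power is 0.865.

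**Power after the fix.** All 106 per arm analysed, with a share e per arm counted as unsuccessful, so success = p·(1 − e):

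| Completer success | e | All-randomized success | Power at 106 | N per arm for 80% |
|---|---|---|---|---|
| 75% / 90% | 5% | 71.3% / 85.5% | 0.81 | 103 |
| 75% / 90% | 10% | 67.5% / 81.0% | 0.73 | 129 |
| 70% / 85% | 5% | 66.5% / 80.8% | 0.76 | 118 |
| 70% / 85% | 10% | 63.0% / 76.5% | 0.69 | 143 |

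**The case against.** The best defence is that many exclusions may be harmless. T4b and M1 findings are features of the tumour, so randomization should balance them; part of the 5% is withdrawal, which need not be related to outcome. Balanced exclusions leave the type I error at 0.05. There are also partial safeguards: a blinded endpoint assessor, video review, individual reporting of omitted dissections, and the dropout comparison. All of this stands as a limit on the likely size. It does not remove the problem, because these measures would make an imbalance visible without restoring the randomized comparison.

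A reader might also infer more than the document supports:

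- *Converted patients are dropped.* The article does not say so. Surgical approach does not mention conversion, and Secondary endpoints counts conversions to thoracotomy, which suggests that these patients are kept. Their status is unclear.
- *The completeness condition removes only palsy patients.* That is one reading. Taken literally, the condition asks for 6-month data from everyone, and a general 6-month visit is planned for all. The dropping of patients who already failed on nodes depends on the same wording.
- *Failure is understated in both arms.* This holds only where excluded patients fail more often than those analysed.

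It could also be said that analysis populations belong in the analysis plan still to be written. Here, however, the article itself fixes the population and builds the 10% inflation around it.

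**Conclusion.** The concern holds: the only stated population depends on post-randomization events that can be related to outcome, and nothing stated prevents those events from differing between arms.

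The size is a range. With 5% excluded on average, the false-positive rate runs from 0.05 (balanced) through about 0.09 to about 0.22. The 0.22 needs both an 8%/2% split and failure in every excluded patient, so it should not be read as the expected error rate. About 0.41 needs the 10% maximum in each arm, with all RE exclusions failing and VATE exclusions average. No split between arms and no failure rate among excluded patients is given in the document.

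Nor should 0.81 be taken as the power after correction. It counts only 5% as failures and uses the more favourable pair of rates; if both expected 5% groups count as failures, power falls below 80% on either pair.

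**What to change.** Make the primary analysis all randomized patients in their assigned arm, with these rules fixed before anyone sees outcome by arm:

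1. Classify at once every patient whose outcome is already determined: no left RLN nodes is unsuccessful; nodes present and no left palsy at week 1 is successful.
2. Count a dissection abandoned for an intraoperative adverse event as unsuccessful.
3. State how conversions are handled: analyse them in their assigned arm by their actual nodes and palsy status.
4. Count week-1 left palsy without a 6-month examination, including death, as unsuccessful. As a sensitivity analysis, use multiple imputation from the 1- and 3-month laryngoscopies.
5. State one rule, the same in both arms, for T4b/M1 patients and for withdrawals before surgery: for example unsuccessful in the primary analysis, with a sensitivity analysis that excludes them.
6. Keep the present population as a supportive per-protocol analysis.

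The cost is wording and one further analysis set, with no new data. The formal analysis plan is still to be prepared under blinding, so the change can be made there and in the protocol. The stated 80% power must be rechecked and restated across the range in the second table; the sponsor should then either accept the lower figure openly or revisit the number enrolled.

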### Secondary endpoints

Secondary endpoints will include: the number of nodes removed along the right and left RLN; the incidence of pneumonia, defined according to the Revised Uniform Pneumonia Score which includes temperature, leukocyte count, and pulmonary radiography (Table 2) [25]; the incidence of other postoperative complications (e.g., anastomotic leakage, chylothorax), defined according to the Esophagectomy Complications Consensus Group system; the total percentage of surgery-related major postoperative complications (i.e., grade IIIa or higher according to the Clavien–Dindo criteria) [26]; in-hospital, 30-day, and 90-day mortality rates, defined as any death occurring during the same hospitalization and within 30 or 90 days after surgery, respectively; R0 resection rates, defined as microscopically negative proximal/distal and circumferential margins; surgery-related parameters (including thoracic, abdominal, and total surgical time (expressed in minutes); unexpected events and complications occurring during surgery (e.g., massive hemorrhage, perforation of other organs); blood loss during surgery (expressed in milliliters per phase); and number of patients requiring conversion to thoracotomy and related reasons); postoperative recovery parameters (including length of mechanical ventilator use after surgery (expressed in minutes), length of ICU stay (expressed in hours), length of hospital stay (expressed in days), and need for reintubation or readmission to the ICU); quality of life and psychometric measures (including the EORTC QLQ-C30, OES-18, and Hospital Anxiety and Depression Scale (HADS) questionnaires, administered at the following time points: 5 days before surgery; 4 weeks, 3 months, and 6 months after surgery; and on a yearly basis up to 5 years thereafter); and oncological outcomes (including 2-year, 3-year, and 5-year disease-free and overall survival rates).

**Table 2 Tab2:** Revised Uniform Pneumonia Score

Diagnostic criterion	Revised Uniform Pneumonia Score	
	Range	Score
Temperature (°C)	≥ 36.1 and ≤ 38.4	0
	≤ 36.0 and ≥ 38.5	1
Leukocyte count (× 10^9^/L)	≥ 4.0 and ≤ 11.0	0
	< 4.0 or > 11.0	1
Pulmonary radiography	No infiltrate	0
	Diffused (or patchy) infiltrate	1
	Well-circumscribed infiltrate	2

A sum score of 2 points or higher, in which at least 1 point is assigned because of infiltrative findings on pulmonary radiography, indicates the presence of pneumonia

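### The only stated analysis population also governs the secondary outcomes, so operations stopped without RLN dissection and some early deaths leave the safety comparisons

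*Protocol article*

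**What the plan says.** The Statistical analysis section introduces its population with "Data analysis will be performed in patients who will receive RLN LND according to the procedure assigned at randomization" and adds a second condition, "who will have complete follow-up data on nerve palsy recovery status at the 6-month assessment". The sentence is not tied to the primary outcome. The tests for the primary and the secondary outcomes follow in the same paragraph, and no all-randomized, all-operated or safety set is named there or elsewhere in the article.

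The same section budgets for exclusions. On the first condition it says "A small percentage of patients (estimated 5% maximum) are expected not to undergo the procedure assigned at randomization", the reasons being "either because of self-withdraw from the study or because of occurrence of unexpected intraoperative findings", with a cross-reference to the Surgical approach section. A further 5% may be lost to follow-up, for a maximum of 10%.

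Surgical approach states: "The operating surgeon will be exempted from performing RLN LND in the presence of at least one of the following conditions". The conditions are T4b disease, M1 disease, and unforeseen perioperative events or findings that require surgery to be discontinued.

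Secondary endpoints include "in-hospital, 30-day, and 90-day mortality rates, defined as any death occurring during the same hospitalization and within 30 or 90 days after surgery", intraoperative events such as massive haemorrhage or organ perforation, major complications, R0 rate, survival, and the "number of patients requiring conversion to thoracotomy and related reasons".

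Follow-up schedule places the later palsy assessment at "6 months (in the subgroup of patients with confirmed postoperative left side RLN palsy at 1 postsurgical week". It also says that complications, readmissions and deaths to 30 and 90 days will be collected.

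**The concern.** A population built to make the palsy endpoint evaluable is a poor one for safety outcomes, because some safety events themselves cause exclusion. A haemorrhage serious enough to stop the operation before RLN LND is a listed secondary endpoint, and it also makes the patient fail the first condition. A patient with week-1 left palsy who dies on day 60 is a 90-day death, and also fails the second condition.

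The decision to omit RLN LND is made after randomization by a surgeon who cannot be blinded. The trial's hypothesis also expects nerve injury to differ between the arms. Exclusions may therefore differ by arm, and the resulting bias could favour either one. The Background gives the aim as assessing both efficacy and safety of robotic esophagectomy (RE), so the between-arm safety comparison is a stated purpose of the trial.

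**Working it through.** **1. The plan's own figure.** Inputs from Sample size calculation: 95 evaluable per arm, 10% dropout. 95 / (1 − 0.10) = 105.6, rounded up to 106 per arm, 212 in total. This matches the plan. The 10% is the share that the population rule is expected to remove.

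**2. Patients removed at the stated ceiling.**
- Assigned procedure not received: 0.05 × 212 = 10.6. This figure pools self-withdrawals with intraoperative findings, so discontinued operations are some unstated part of it.
- Lost to follow-up: 0.05 × 212 = 10.6.
- Total: 21.2, leaving 212 − 21.2 = 190.8, about 191. The budget has no separate line for deaths.

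**3. Which patients fail, condition by condition.**
- *Operation discontinued without RLN LND:* fails the first condition on any reading, and the section itself counts these patients as dropouts.
- *Death before the week-1 laryngoscopy:* palsy status is never established, so the data are not complete.
- *Death before 6 months with left palsy at week 1:* the scheduled 6-month assessment is missing, so the second condition fails.
- *Death before 6 months without palsy at week 1:* no 6-month assessment is scheduled, so the patient can reasonably count as complete and stay in.
- *Conversion to thoracotomy:* the text does not say whether RLN LND was then received according to the assigned procedure. Conversion is not among the listed reasons.

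**4. Deaths lost.** The article gives no mortality rate. Assumptions: 90-day mortality 1–5%; share of deaths in patients with week-1 palsy equal to the Background palsy range of 20–80%, with palsy and death independent. That range is not limited to the left side, so it is only a rough guide.
- Deaths per arm: 106 × 0.01 = 1.06 to 106 × 0.05 = 5.3.
- Lost per arm: 1.06 × 0.20 = 0.2 to 5.3 × 0.80 = 4.2, plus any deaths before laryngoscopy.

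**5. Effect on reported mortality.** Let d = 106 × true rate and q = share of deaths removed. Assume another 5% of the arm (5.3 patients), all survivors, is excluded. Observed rate = d(1 − q) / (106 − 5.3 − dq). VATE is the thoracoscopic arm.

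| q | True 3% in each arm | True 2% RE, 5% VATE | Observed difference |
|---|---|---|---|
| 0 | 3.16% | 2.11%, 5.26% | 3.2 points |
| 0.20 | 2.54% | 1.69%, 4.26% | 2.6 points |
| 0.80 | 0.65% | 0.43%, 1.10% | 0.7 points |

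With the rates exchanged between arms the difference shrinks in the same way, so an excess of deaths under RE would be understated equally.

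**The case against.** Five points can be made for the plan.

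- **Mortality is not zero by construction.** A reader might infer that, since nobody who dies by day 90 can attend at 6 months, 30-day and 90-day mortality must be 0% in both arms. The documents do not support this. If everyone needed a 6-month examination, every living patient without palsy would be excluded too. Even at the top of the Background palsy range that is 20% of an arm, 0.20 × 106 = 21, against the 106 − 95 = 11 that the sample size allows. This objection stands.
- **Conversions are not shown to be excluded.** A reader might infer that they are. But conversion appears neither in the Surgical approach exemptions nor in the dropout reasons, and counting conversions as an endpoint suggests that these patients are meant to be kept. This stands; the text is only unclear.
- **Analysis sets belong in the statistical analysis plan, which is still to be written.** This holds for missing detail. Here, however, the article states a general rule, and a later plan naming another set would depart from it. The sentence itself needs limiting.
- **Harm would still be visible.** Early events are collected, dropouts are compared with completers, and the Data Safety Monitoring Committee sees individual charts every 50 patients. So it would be too strong to say that an excess of harm would go unseen. But dropouts versus completers is not a comparison of randomized arms, and the Interim analysis section adopts no formal stopping rule for harm. None of this restores the final between-arm comparison.
- **The numbers are small.** Discontinued operations fall within a 5% maximum. That is true, but mortality and serious intraoperative events are themselves rare, so a few exclusions matter.

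**Conclusion.** The concern holds in a limited form. The rule as worded covers the secondary outcomes. It removes discontinued operations from the comparisons that should count them, and it removes at least the deaths before the week-1 laryngoscopy and those among patients with week-1 left palsy. It does not make early mortality zero, and exclusion of converted patients is an open question of wording.

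The size is bounded by the plan's own 10%, about 21 of 212 patients. The loss of roughly 0.2 to 4.2 deaths per arm rests on assumed 90-day mortality of 1–5%, palsy of 20–80%, and independence of the two. If palsy raises the risk of death, as the Background's link to pulmonary complications makes plausible, the share of deaths lost would be larger than the palsy rate. The direction of bias between arms cannot be told from the documents.

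**What to change.** In Statistical analysis, limit the population sentence to the primary endpoint and add text such as: *Mortality, complications, conversion, intraoperative events, R0 rate and survival will be analysed by assigned arm in all randomized patients (perioperative endpoints: all randomized patients who start surgery), irrespective of conversion, completion of RLN LND or availability of the 6-month laryngoscopy.* This also settles the status of converted patients for these outcomes.

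The cost is small. No new visits are needed, since early complications, readmissions and deaths are already to be collected. Some data, survival in particular, will be missing for patients who withdraw; the number and reasons should be reported by arm. Whether the completer set should remain the population for the primary endpoint is a separate issue that this change leaves open.

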## Methods/design

### Design and setting

A study flowchart is shown in Fig. 1. This is an investigator-initiated, investigator-driven multicenter, open-label, randomized controlled trial (termed REVATE) enrolling patients with ESCC scheduled to undergo LND along the RLN. Patients will be randomly assigned (1:1 ratio) to undergo minimally invasive esophagectomy (MIE) with either RE or VATE. All participating surgeons will be required to have competence with both techniques. The study will take place in two high-volume surgical centers located in Taiwan and China, and will be conducted with adherence to the principles of the World Medical Association’s Declaration of Helsinki.

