### Sample size calculation

Based on a preliminary study conducted by our group, the projected rates of successful left RLN LND (according to the definition proposed in the current trial) are 70–75% and 85–90% for VATE and RE, respectively [20]. The purpose of our study is to demonstrate that the rate of successful left RLN LND will be at least 15% higher for RE compared with VATE (based on a conservative 75% rate for VATE). Because our null hypothesis is that the difference between the two arms is ≤15%, we will adopt one-sided testing. In a one-sided test, the “extreme” portion of distribution is decided beforehand as meaning “sufficiently large” (i.e., 15% in our case) [20]. Assuming an alpha error of 0.05 and an 80% power using one-sided two-sample comparisons of proportions under a balanced trial design, a total of 95 patients per treatment arm will be required. Assuming a dropout rate of 10% in the entire study cohort, we plan to enroll a total of 212 patients (i.e., 106 in each arm).

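### Randomization is stratified by hospital but the named primary test ignores hospital; the effect is slight conservatism, and the plan should name one hospital-stratified primary test

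*Protocol article*

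**What the plan says.** All statements are in the Protocol article.

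- Design and setting: "The study will take place in two high-volume surgical centers located in Taiwan and China", with 1:1 allocation.
- Randomization: "patients will be stratified in a 1:1 fashion according to the enrolling hospital", using permuted blocks of varying size. The stated reason is to limit confounding by local treatment factors, with postoperative care as the example.
- Statistical analysis, primary outcome: "The primary outcome will be analyzed using a two-sample proportion test (single-sided". No hospital term is given.
- Statistical analysis, near the end of the same section: "The Cochran–Mantel–Haenszel test will be used to examine the differences in categorical outcomes between the two treatment groups after adjusting for study center". The sentence names nCRT as a second adjustment factor. It does not say whether the primary outcome, itself binary, is among those outcomes. It gives neither the sidedness of the test nor its rank against the proportion test.
- Sample size calculation: 95 per arm from a one-sided, two-sample comparison of proportions, with no stratification.

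**The concern.** Blocking within hospital keeps the arms balanced in each hospital, so a difference in success rate between hospitals largely cancels out of the treatment comparison. The pooled standard error of the two-sample test still contains that variation. When the hospitals differ, the standard error is too large, the true type I error falls below the nominal 5%, and a little power may be lost.

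There is also a question of clarity. A reader can take the CMH sentence as covering the primary outcome. The plan would then hold two tests of one endpoint in an open-label trial, without an explicit statement of how they relate.

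This is not a detail left open for the analysis plan. The article names the primary test, so a later document would have to override that sentence.

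**Working it through.** **1. The plan's own figure.** Inputs from Sample size calculation: projected success rates that "are 70–75% and 85–90% for VATE and RE, respectively", a one-sided alpha of 0.05 and 80% power. The formula is n = [z₀.₉₅·√(2p̄(1−p̄)) + z₀.₈₀·√(p₁(1−p₁)+p₂(1−p₂))]² / (p₂−p₁)².

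With 70% vs 85%, p̄ = 0.775:
- √(2×0.775×0.225) = 0.5906, times 1.645 = 0.9714
- √(0.2100+0.1275) = 0.5809, times 0.8416 = 0.4889
- n = (0.9714+0.4889)² / 0.0225 = 94.8, so 95 per arm
- 95/0.90 = 105.6, so 106 per arm and 212 in total

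The stated size is reproduced with a null of zero difference and no stratification. The control rate that the text names (75%, hence 75% vs 90%) gives 79, so the check below uses 70% vs 85%.

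**2. Type I error by hand.** Assume two equal hospitals whose success rates lie d apart around 70%, and no treatment effect. The pooled variance per patient is 0.70×0.30 = 0.21. The within-hospital variance, which drives the treatment difference under blocking, is 0.21 − d²/4. The effective cut-off is 1.645/√(ratio of within-hospital to pooled variance).

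| Gap d | Within-hospital variance | Ratio | Effective cut-off | One-sided error |
|---|---|---|---|---|
| 0 | 0.2100 | 1.000 | 1.645 | 5.0% |
| 10 points | 0.2075 | 0.988 | 1.655 | 4.9% |
| 20 points | 0.2000 | 0.952 | 1.685 | 4.6% |
| 30 points | 0.1875 | 0.893 | 1.741 | 4.1% |

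**3. Simulation.** 400,000 trials per cell; 48 + 47 patients per arm in two hospitals; a common odds ratio set to give a 15-point overall difference (70% vs 85%). The pooled z test is compared with the CMH test stratified by hospital, both one-sided at 0.05 and without continuity correction.

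| Gap (assumed) | Type I error, unstratified | Power, unstratified | Power, CMH | Change in power |
|---|---|---|---|---|
| 0 | 5.1% | 81.1% | 80.6% | −0.5 |
| 10 points | 5.0% | 81.0% | 80.8% | −0.2 |
| 20 points | 4.7% | 81.3% | 81.7% | +0.4 |
| 30 points | 4.1% | 81.8% | 83.2% | +1.4 |

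The CMH test stays at about 5.0% throughout. A 70:30 split of patients between hospitals gives nearly the same figures. At 75% vs 90% the pattern is the same: 87.4% vs 87.1% with no gap, 88.5% vs 89.8% at 30 points.

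**4. Why sidedness matters.** Only the proportion test is described as single-sided. If the CMH test were read as two-sided (an assumption), the cut-off would be 1.96. Approximate power at 70% vs 85% would be Φ[(0.15×√95 − 1.96×0.5906)/0.5809] = Φ(0.524) = 70%. The same formula with 1.645 gives 80%. In roughly one trial in ten the two tests could then fall on different sides of significance.

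**The case against.** The strongest reply is that both tests are valid and the difference is trivial. An unadjusted primary test backed by a prespecified adjusted one is an ordinary plan, and here it matches the sample-size method. In every simulated case the unstratified test keeps more than the planned 80% power. Its error is on the safe side. No hospital gap is documented; both centers are high-volume, surgeons need at least 50 previous procedures, and the reason given for stratifying concerns postoperative care rather than node retrieval or nerve palsy. All of this stands, and it limits the size of the point. It does not remove the mismatch between how patients are randomized and how the primary outcome is tested.

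Two objections bear on the remedy, and both are right:

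- nCRT is not a randomization stratum, so the argument from design covers hospital only. With four strata (hospital by nCRT, assuming 50% nCRT with no prognostic effect), power was 81.0% unstratified vs 80.2% stratified at no gap, 81.2% vs 80.7% at 10 points and 81.3% vs 81.4% at 20 points.
- The CMH test addresses a null of zero difference. It does not test the null worded in Sample size calculation, a difference of at most 15%.

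A reader might infer that the plan wastes material precision, or that the primary result would be unreliable. The documents do not support either: the loss is nil or negligible unless the hospitals lie some 20 to 30 points apart. Nor do they show that the CMH test is meant as a rival primary test, or merely as an additional one; the text does not rank it.

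**Conclusion.** The point holds and is minor. The named primary test leaves out the factor by which patients are randomized. If the hospitals differ in success rate, the test is mildly conservative; false positives do not increase. A hospital-stratified test holds its level in all cases examined, and costs no more than about half a power point when the hospitals are alike. The figures rest on assumed gaps, two hospitals, 95 analyzed patients per arm and a common odds ratio.

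The clearer gain is in wording: one sentence should settle which test decides the primary outcome and that it is one-sided.

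Two discrepancies in Sample size calculation are separate from this point: the worded null of at most 15%, and the stated 75% control rate that does not yield 95.

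**What to change.** In Statistical analysis, name a single primary analysis: a one-sided CMH test at 0.05 stratified by enrolling hospital, reported with the Mantel–Haenszel risk difference and its confidence interval. Label the unstratified proportion test, and the CMH version that also adjusts for nCRT, as sensitivity analyses. Confine the general CMH sentence to secondary outcomes or state its role there.

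The cost is a sentence or two. Hospital is already recorded and the test already planned, so no new data are needed, and the sample size can stay as it is.

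This assumes a null of zero difference, the one that reproduces 95 per arm. If the investigators do mean to test against a 15-point margin, CMH will not serve. They would need the hospital-stratified risk difference compared with that margin, and the sample size would have to be reworked.
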